### Methods for analysis of intervention and further activity outcomes

Mean/median compliance and adherence rates with standard deviations/inter-quartile ranges will be reported overall and for each week of the intervention period. Additionally, reasons for not attending or aborting a training session will be summarised. Mean/median ratings of perceived motor-cognitive task difficulty and perceived performance with standard deviations/inter-quartile ranges will be reported overall and for each week of the intervention period. These will be compared to the targeted ranges for task difficulty and perceived performance to establish if an optimal training load was achieved. The volume of usual care (physical, cognitive, and other therapies) and general physical as well as cognitive activities will be descriptively summarised and considered as covariates in the LMEMs of the primary and secondary analyses.

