### Intervention description {11a}

The intervention group receives concept-guided, personalised, motor-cognitive exergame training additionally to usual care. The personalised motor-cognitive exergame training for stroke (PEMOCS) concept, which guides the intervention, was developed specifically for this study and, in accordance with the Modified Consensus on Exercise Reporting Template (CERT) for Therapeutic Exercise Interventions [78, 79], published elsewhere [80]. It determines the training dosage with regards to frequency, intensity, time, type, and volume of the exercises, which are based on recommendations from scientific literature for motor-cognitive and exergame trainings in chronic stroke and healthy older adults. Participants train twice a week for 12 weeks (intervention period, see Fig. 1). Training sessions last between 30 (beginning) and 40 (end) minutes, progressing in duration for 2 min every second week and resulting in 840 min total planned training time (see Table 1). Additionally, the PEMOCS concept is designed to provide personalised progression and variability in training considering principles for neuroplasticity, motor learning, and training [80–83]. It was developed based on Gentile’s Taxonomy for motor learning [84] and tested for its feasibility in the target population [85]. In short, motor and cognitive tasks of the exergame training are allocated to various difficulty levels along a skill-progression scheme with three dimensions. Based on the participants’ subjective ratings of their perceived motor-cognitive task difficulty and their perceived performance (see ‘Intervention outcomes’), progression through the difficulty levels is determined individually for each participant. Therefore, the training is personalised within a standardised progression scheme. Additionally, variability rules ensure variation in training tasks.

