**Intervention outcomes**	
Compliance rate (overall)	$$={\text{Mean}} \frac{\text{Number of attended training sessions}}{\textrm{ Number of offered training sessions}} \times 100$$
Compliance rates in each week (1–12)	
Adherence rate (overall)	$$={\text{Mean}} \frac{\text{Total attended training time}}{\textrm{ Total offered training time}} \times 100$$
Adherence rates in each week (1–12)	
Reasons for not attending or aborting a training session	
Perceived motor-cognitive task difficulty (overall)	Collected by visual analogue scale
Perceived m-c-task difficulty in each week (1–12)	
Perceived performance (overall)	Collected by visual analogue scale
Perceived performance in each week (1–12)	

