### Intervention and further activity outcomes

Compliance and adherence to the trainings and the reasons for not attending or aborting a training session are recorded during the intervention period (T0–T1, see Table 2, Figs. 1 and 3). Additionally, participants in the intervention group are asked to rate the motor-cognitive task difficulty of the training tasks (perceived task difficulty, PTD) and their motor-cognitive performance (perceived performance, PP) in every training session (during T0–T1, see Table 2, Figs. 1 and 3). Visual analogue scales (VAS) in the eCRF based on the cognitive load theory [130] and the NASA-TLX [National Aeronautics and Space Administration Task Load Index [131]] are used to collect these ratings (Additional file 1). PTD and PP are expressed as percentage values where higher percentages stand for more difficult tasks and better performance, respectively. The intervention outcomes are summarised in Table 4.

All participants are interviewed weekly throughout the whole study (T0–T2, see Table 2, Figs. 1 and 3) regarding the dose (frequency and time) and content (intensity and type) of moderate to intense physical and cognitive activities, which they perform as part of their usual care or in their leisure time. Definitions for moderate to intense activities are based on the World Health Organisation’s (WHO) 2020 Guidelines on Physical Activity and Sedentary Behaviour [132]. The interviews are done using a structured questionnaire (Additional file 1), which implies the FITT-VP principles [70] and the TIDieR checklist [Template for Intervention Description and Replication [133]]. The further activity outcomes are summarised in Table 4.

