## Sample size {14}

A sample size of 38 participants (approx. 19 per group) was estimated for this study. The sample size estimation was based on systematic reviews investigating the effects of motor-cognitive training and exergames on cognitive functions. Stanmore et al. included studies with any population (including five out of seventeen studies with stroke or other neurological patients) and found a small to medium effect for global cognitive functioning (SMD = 0.44, *p* = 0.001) and several small to large effects for cognitive domains including executive functions, processing speed and visuospatial skills (0.26 ≤ SMD ≤ 0.90, *p* < 0.05) (132). Five further reviews included studies with older adults and found small to large effect sizes for global or overall cognitive functioning and cognitive domains including attention, executive functions, learning and memory, and processing speed (0.30 ≤ SMD ≤ 1.37, *p* < 0.05) [31, 35, 54, 56, 134]. Based on this evidence, a small to medium effect on global cognitive functioning is anticipated for the planned study (*f* = 0.21). The sample size was estimated using G*Power, entering this effect size (requiring no expected difference between groups and standard deviations) and the following parameters into the mask for a two-way mixed ANOVA; α-level = 0.05, power = 0.80, number of groups = 2, number of measurements = 3, correlation among rep measures = 0.5, nonsphericity correction = 1. Dropouts will be replaced by post-recruitment until the planned sample size is achieved. Based on the recent feasibility study [85] and comparable literature [135–137], a dropout rate of 10–20% can be expected.

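### The training-load conclusion rests on group mean or median ratings, although load is set person by person and no in-range share is planned

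*Protocol article*

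**What the plan says.** *Intervention description {11a}* makes the load individual. From the participant's ratings of task difficulty and of own performance, "progression through the difficulty levels is determined individually for each participant". *Intervention and further activity outcomes* says that both ratings are taken on visual analogue scales in every training session, in the intervention group only, and that "PTD and PP are expressed as percentage values where higher percentages stand for more difficult tasks and better performance, respectively".

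*Methods for analysis of intervention and further activity outcomes* then fixes the summary: "Mean/median ratings of perceived motor-cognitive task difficulty and perceived performance with standard deviations/inter-quartile ranges will be reported overall and for each week". The next sentence fixes the use made of it: "These will be compared to the targeted ranges for task difficulty and perceived performance to establish if an optimal training load was achieved".

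Table 4 lists the two ratings overall and for each of weeks 1 to 12. Neither place plans a count or percentage of participants or sessions within range. The range limits are not in the article, which refers to a separate publication for the training concept.

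**The concern.** The question is whether each person trained at the intended load. The planned summary answers whether the group's centre did. Under-loaded and over-loaded participants offset each other in a mean. A median likewise says nothing about how far, or how many, others lie from it. Weekly summaries stop early weeks from offsetting late ones, but they do not stop one participant offsetting another within the same week.

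The two ratings are also summarised separately. A session can be in range for difficulty and out of range for performance, and two separate summaries cannot show how often that happens.

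What is at stake is the trial's statement about delivery of its personalised training. The introduction names missing personalised progression as a weakness of earlier studies, and the discussion expects the results to inform on its benefits. The comparison with the targeted ranges is the only analysis in the article that checks whether the individualised load was reached.

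**Working it through.** The article states no figure on this point, so there is none to reproduce.

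**Inputs from the article.** Ratings are percentages taken every session. The intervention arm has about 19 participants (*Sample size {14}*). The summaries are mean or median with SD or IQR, overall and weekly.

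**Inputs assumed.** The half-width *h* of the target range, the between-person SD *s*, normally distributed person means, and a group mean exactly at the centre of the range. None of these is in the article.

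**Step 1. Share outside when the centre is ideal.** The share inside is 2Φ(*h*/*s*) − 1, and the share outside is one minus that. For *h* = 10:

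- *s* = 10: 2Φ(1.000) − 1 = 0.683, so 32% outside
- *s* = 15: 2Φ(0.667) − 1 = 0.495, so 50.5% outside
- *s* = 20: 2Φ(0.500) − 1 = 0.383, so 62% outside

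Percentage outside over a wider set of assumptions:

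| Half-width | SD 10 | SD 15 | SD 20 | SD 25 |
|---|---|---|---|---|
| 5 points | 62 | 74 | 80 | 84 |
| 10 points | 32 | 50.5 | 62 | 69 |
| 15 points | 13 | 32 | 45 | 55 |

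Half the participants are outside when *h*/*s* = 0.6745, that is, when *s* = *h*/0.6745 ≈ 1.48*h*. A majority outside therefore needs an SD above about 1.48 half-widths.

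**Step 2. An extreme case at the trial's arm size.** Take 19 participants and an assumed range of 50 to 70. Put nine at 40, one at 60 and nine at 80.

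- Mean = (9×40 + 60 + 9×80)/19 = 1140/19 = 60, and the median is 60. Both are inside.
- Outside the range: 18/19 = 95%.
- SD = √(18×20²/18) = 20, and the IQR is 40 to 80.

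The centre looks ideal. The spread, if consulted, shows the failure.

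**Step 3. Whether the planned spread settles it.** If the whole IQR had to lie inside the range, about half or more of the summarised values would be inside, and a majority failure on that rating could not occur. The article states neither this rule nor any other use of the SD or IQR. It also does not say whether the spread is taken over person means or over single sessions.

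**Step 4. Both ratings together.** Suppose each rating, taken alone, is in range in 68.3% of sessions (the figure from Step 1 at *h* = *s* = 10, borrowed for illustration). The share with both in range can then lie anywhere from 2×0.683 − 1 = 36.6% to 68.3%. Separate means, medians, SDs and IQRs do not narrow this interval.

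**The case against.** The strongest reply is that the plan already reports the spread. The SD or IQR stands in the sentence just before the comparison, and the word that opens the comparison can be read as covering the whole summary. In the Step 2 example that spread would give the problem away. This stands in large part: the plan does not hide variation. It does not supply the share of participants or sessions in range, or joint attainment on both ratings.

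A reader might infer that the plan would declare an optimal load when most participants had missed it. The documents do not support that. They state no pass rule, so a judgement on the centre alone is one reading, not the stated method. Under the assumptions above with half-width 10, 68% are still inside at SD 10 and only SD 20 gives a clear majority outside. Nothing in the article shows that such an SD is likely.

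A reader might also infer that too-easy early weeks are averaged against too-hard late ones. Weekly summaries are planned, so this does not hold for the check as a whole.

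A third inference is that the difficulty level reached is the true load and is wrongly missing from Table 4. The article measures load by perception, which is a legitimate target when the same level may be easy for one person and hard for another. It also does not say that the level is recorded.

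Finally, in-range tables might be thought detail that an article leaves to the full protocol or analysis plan. That would answer a complaint of omission. Here the article itself names the statistic, the comparator and the conclusion to be drawn, and the point concerns that stated choice. Individual classification is not foreign to the plan: *Methods for additional analysis {20b}* uses an adherence cut-off per participant and separates responders from non-responders.

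**Conclusion.** The concern holds in a limited form. The load conclusion is drawn from group summaries although load is individual. A centre within range is compatible with a substantial share of participants outside it. The planned SD or IQR would hint at this but has no stated role in the judgement, and separate summaries cannot show whether both ratings were in range in the same session.

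Its size cannot be computed from the article. The tabulated shares, 13% to 84% outside, depend wholly on the assumed half-width, SD, normality and perfect centring, and they show what is possible rather than what is expected.

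The consequence is modest. This is a descriptive process measure in about 19 participants. It does not enter the MoCA model, the sample size or the per-protocol set, which is defined by withdrawal and adherence. The article plans no analysis relating MoCA change to load, so the primary result does not depend on this point.

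**What to change.** In *Methods for analysis of intervention and further activity outcomes* and in Table 4:

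1. Define for each participant the percentage of attended sessions in which perceived task difficulty and perceived performance both lay within their targeted ranges. Base the load conclusion on this measure and report its distribution.
2. For each week, report the percentages below, within and above range.
3. Keep the mean or median ratings with SD or IQR, overall and weekly, as description.
4. Report the difficulty level reached by week only if it is already recorded.

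The cost is a few lines of extra descriptive analysis. The ratings are already collected in every session, so items 1 to 3 need no new data. Nothing changes in the training, the primary analysis, the power or the per-protocol set.

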### Interim analysis {21b}

N/A. No interim analyses are planned, as preliminary analysis of the effect will most probably be underpowered and, therefore, not informative for the decision of an early study termination.

### Methods for additional analysis (e.g. sub-group analyses) {20b}

As the ITT analyses may underestimate a present treatment effect [148], the analyses of the primary and secondary outcomes will be repeated with only those participants, who did not withdraw from the study within the intervention period (T0–T1), and with adherence rates of ≥ 85% (per protocol analysis). This cut-off was chosen based on systematic reviews covering comparable interventions, outcomes, and populations [27, 151], where a minimum of 720 min in at least 12 weeks or an intervention duration of at least 8 weeks were recommended. Moreover, 85% of 24 training sessions results in an ‘acceptable’ absence of 3.6 sessions, which seems practical to account for sickness and conflicting schedules. The results of the ITT and per-protocol analyses will be compared in the discussion of the study report.

Furthermore, to assess clinical meaningfulness of possible treatment effects, the following analyses will be performed on outcomes that (a) revealed a significant between group effect at either T1 or T2 [152, 153] and (b) a clinically important difference is reported in literature. On the one hand, the difference in change score between the two groups will be compared to clinical meaningful change scores (e.g. 1.22 points in the MoCA [99]). On the other hand, frequencies of ‘responders’ (individual change score above clinically meaningful change) and ‘non-responders’ (individual change score below clinically meaningful change) between the two groups will be compared [152, 153].

### Plans to give access to the full protocol, participant-level data, and statistical code {31c}

The full protocol of this study was published on https://clinicaltrials.gov (NCT05524727). De-identified participant-level data and the statistical code will be available from the corresponding author on reasonable request.

## Oversight and monitoring

### Composition of the coordinating centre and trial steering committee {5d}

Recruitment and screening are performed at all study cites by the (local) principal investigators or their delegated staff. All other study-related procedures are performed by trained members of the sponsor/principal investigator team, who are in daily contact regarding the organisation of the trial.

### Composition of the data monitoring committee, its role and reporting structure {21a}

Data monitoring in this study is performed by a senior researcher not otherwise involved in the study procedures. On at least three monitoring visits, the monitor reviews the study (team) documents and regulatory aspects, the enrolment process, the participant data, safety aspects, and protocol deviations. Upon monitoring visits, the monitor generates a report including any findings that must be resolved. Resolution of these findings is performed by the principal investigator. Additionally, the clinical trial centre (CTC) of the University Hospital Zurich performs a quality visit on the protocol and monitoring reports. Both the monitor and the clinical trial centre are independent of the sponsor.

### Adverse event reporting and harms {22}

Adverse events are recorded in the eCRF throughout the study and managed according to GCP guidelines.

### Frequency and plans for auditing trial conduct {23}

The project management group (including study staff from all sites) meets at least weekly to track correct trial conducted. As this is a low-risk study, no data monitoring committee exists; however, according to the approved study protocol by the cantonal ethical committee, an independent monitor performs at monitoring visits on the study documentation and procedures, including but not limited to the following actions:An initiation visit before the study start, where is evaluated whether ethical approval is granted, training of study staff was performed and documented, study and safety documentation as well as case report forms were appropriately prepared, and insurance is valid;At least one routine monitoring visit (further visits are planned if indicated due to inconveniences), where it is checked whether protocol and study documentation is up-to-date, informed consent procedures and enrolment are correctly performed, source data is correctly filed and data transferred to case report forms, safety is correctly reported and treated, and blinding has been maintained; andA closure visit upon the end of the study, where the monitor repeats the checks from the routine monitoring visit, and additionally assesses whether documentation is complete and archiving appropriately prepared.

### Plans for communicating important protocol amendments to relevant parties (e.g. trial participants, ethical committee) {25}

Necessary protocol amendments are submitted to the ethical committee before implementation. All study-team members are informed about changes to the protocol on the weekly project management group meetings. Updated versions of the protocol are added to the investigator site files upon approval of the ethical committee. In case of an amendment, which changes study procedures or conditions for participants, participants are informed immediately and the clinical trial registry is updated upon approval of the ethical committee.

## Dissemination plans {31a}

The findings of this study will be published in scientific journal articles and scientific presentations. All publications will be authored by the study team, following established authorship guidelines. Participants will receive a copy of their individual study data upon request.

## Discussion

The PEMOCS study evaluates the effect of a 12-week concept-guided, personalised, motor-cognitive exergame training added to usual care compared to usual care alone on global cognitive functions and explores effects on specific cognitive functions, health-related quality of life, and gait in chronic stroke survivors. The results will give insight into under-investigated research topics in chronic stroke: the effect of a motor-cognitive exergame integrating whole-body movements on cognitive functions, its effect on spatiotemporal gait parameters relevant in stroke, and the benefits of personally-tailored progression and variability in exergame interventions [37]. The feasibility trial preceding this RCT showed that chronic stroke survivors were continuously motivated for and satisfied with the personalised exergame training and adherence was high [85]. Therefore, satisfactory adherence in the training group is expected in this study. Based on results from studies with exergame trainings in healthy older adults or other neurological patients, superior effects on cognitive functions of the additional exergame training compared to usual care alone are hypothesised [34, 63, 154]. We expect most participants with chronic stroke to exhibit cognitive decline, as cognitive impairment is widely reported in chronic stroke, even in patients with seemingly good clinical outcome [155, 156]. We found significantly lower MoCA values in a high-functioning stroke sample compared to healthy adults with comparable age in a previous study [129]. We did not, however, include a MoCA-based threshold for cognitive impairment for inclusion because such a screening instrument seems unsuitable to identify subtle or specific cognitive deficits [76]. Furthermore, previous research has shown that exergame training may have positive effects on gait and mobility [37, 67], including gait speed, spatiotemporal gait parameters, and mobility in chronic stroke. Therefore, superior improvements in various spatiotemporal gait parameters and mobility in the intervention compared to the control group are expected in this study.

The findings of this study could be considered for the design and prescription of future long-term rehabilitation interventions for chronic stroke survivors that focus on cognitive functioning next to restoring motor functions. This is an identified need since cognitive dysfunction after stroke has a persistently high prevalence [157–159]. Exergames have the potential to increase motivation for training [42, 85], to produce additional benefits on physical functions as compared with conventional care modes [60, 67], as well as on cognitive functions [55, 63, 154]. Exergames that contain aspects of virtual reality have shown to be able to significantly effect on *Body Structure/Function* and *Activity* level outcomes, including improvements in cognitive function, and there is, therefore, evidence supporting the use of such interventions as an adjunct for stroke rehabilitation [160, 161]. Therefore, exergames could help expand existing rehabilitation services for chronic stroke survivors, which may lead to further improvements of cognitive and motor functioning and, therefore, contribute to increased quality of life after stroke [162].

Due to its design, this study will have two major limitations. (1) Study participants will train 840 min with 100% adherence rate, which is at the lower border of recommended training volume for improving cognitive functions in chronic stroke and older adults [23, 27, 163, 164]. Similarly, some authors recommend more than two and longer sessions per week [55, 164]. However, practical reasons including that participants needed to come into the study centre twice a week limited more training time in this study. Moreover, the feasibility study preceding this RCT showed that participants preferred two sessions per week, lasting 30 to 40 min and no longer [85]. To prevent over-request of time expenditure of the participants and, thereby, harm recruitment, the total training volume was kept at this lower border of recommended time. (2) The black box of usual care and leisure time physical and cognitive activities may influence the measured outcomes as well. Usual care is a wide term and has been reported to include a wide range of interventions, doses, intensities, and implementations [165, 166]. This limitation is addressed by recording the participants’ usual care and general activities besides the study intervention and by considering this in the analysis. (3) This study’s sample size was not based on a standard RCT sample size calculation, as at the time of planning, no expected values for difference between groups and standard deviations for the MoCA in chronic stroke were available due to the novelty of the topic in research. Therefore, the sample size was estimated based on effect sizes from systematic reviews in related literature (see the ‘Sample size’ section).

